**Fig 4 pone.0268535.g004:**
[figure not shown]
System specification of high-performance computer. Republished from [31] under a CC BY license, with permission from ITS, HKU, original copyright 2022.

#### Deep-learning methods

The following deep-learning methods/algorithms will be adopted for the training process:

**Voxel-based:** This method first partitions the 3D model into regular cubes and then inputs into the neural network (Fig 5A). In this study, the 3D vertices are sampled into 64x64x64 voxels. Example of this algorithm is VoxNet, an architecture that integrate a volumetric occupancy grid representation with a supervised 3D Convolutional Neural Network (3D CNN) [32].

**Fig 5 pone.0268535.g005:**
[figure not shown]
A. Illustration of voxel-based method. B. Illustration of view-based method. C. Illustration of point-based method.

**View-based:** This method uses multiple 2D image views of a 3D model for its alignment and orientation (Fig 5B). In this study, 2D image views of resolution 1920x1200 pixels are aggregated from a loop around the 3D models and 2D deep learning framework is applied to them. Example of this algorithm is Group-view convolutional neural networks (GVCNN), which is composed of a hierarchical view-group-shape architecture for 3D-shape representation [33].**Point-based:** This method uses point-cloud to represent the 3D models (Fig 5C). A point-cloud is a set of data points in space. Each point has its set of *x*-, *y*- and *z*-coordinates. Point-clouds are generally produced by 3D scanners, and they measure many points on the external surfaces of objects around them. PointNet++ is an example of such algorithm and it functions by applying PointNet, a deep-learning method on point sets, on a nested partitioning of the inputting point sets [34].**Fusion methods:** This method learns on multiple types of data (multi-view, point-cloud and voxel) and fuses their features. Example of this algorithm is FusionNet, which uses the volumetric grid and multi-view for classification, combining several advances in machine learning of recent years with a summation-based skip connection [35].

#### Presence of antagonist teeth models

The presence of antagonist teeth models are currently essential to the CAD design and the fabrication of the dental prostheses. These antagonist models provide the information of occlusal contacts and limits the cuspal height of occlusal morphology [25]. It is unknown if the same is applied to the AI learning and predicting of the occlusal morphology. Features of the remaining teeth of an arch may be sufficient for the prediction of single missing tooth. Maxillary teeth models with and without the antagonist mandibular teeth models will be used to train the AI system (Fig 6A–6C). Additional mandibular teeth model as well as the MIP maxillomandibular relationship will be input to the AI system.

**Fig 6 pone.0268535.g006:**
[figure not shown]
A & B: Example of a maxillary teeth model (left) and a mandibular teeth model (right). C: Demonstration of maxillary teeth model and its antagonist mandibular teeth model at maximal intercuspal position.

#### Validation of AI system

Separate (50) sets of the original and the processed maxillary teeth models will be serve as validation sets. The effectiveness of the four deep learning algorithms in predicting the occlusal morphology and 3D position of single missing tooth (tooth 16) on the processed models will be evaluated and compared to the natural tooth 16 on the original models.

After determining the appropriate GAN algorithm, the need of antagonist mandibular teeth models in AI predicting the occlusal morphology and 3D position of single missing maxillary tooth will be evaluated.

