**Fig 1 pone.0268535.g001:**
[figure not shown]
SPIRIT diagram showing the schedule of enrollment, allocation, interventions, and assessments of this study. –t_1_  =  baseline assessment (before randomization), 0 (t_0_) = randomization, t_1_ = after randomization, t_2_  =  25% of collected models learnt by AI, t_3_  =  50% of collected models learnt by AI, t_4_ = 75% of collected models learnt by AI, t_5_  =  100% of collected models learnt by AI, t_6_ = the whole study is completed.

Maxillary and mandibular dentate teeth models will be collected from at least 250 volunteers [27], consisting of patients attending the University teaching hospital (Prince Phillip Dental Hospital) as well as the students of the University of Hong Kong. Participants will be screened and selected according to the following inclusion and exclusion criteria:

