**Fig 2 pone.0268535.g002:**
[figure not shown]
General flow of processing collected data.

Collected teeth models will be randomly divided into **training** and **validation** sets.

At least two-hundred **training** sets including the **original** and the **processed** models will be input into the AI system to learn the relationship between individual teeth (tooth 16) and rest of the dentition via a 3D Generative Adversarial Network (GAN) designed for this study (Fig 3). Data will be computed by the High-Performance Computer provided by the Information Technology Services (ITS), The University of Hong Kong (HKU), which is capable of conducting data intensive and accelerated computing using a high-performance computing cluster with an aggregating processing power of 804 TFlop/s (Fig 4).

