### Outcome measurement

The progress of the AI training will be evaluated with quartiles analysis. The following indicators of AI-designed prostheses will be examined at least 4 times during the training procedure, when 25%, 50%, 75% and 100% of collected teeth models have been learned respectively by the AI system. The morphology, i.e., geometric morphometric, and 3D positions, of tooth 16 designed by the trained AI system will be assessed by comparing to the corresponding natural teeth among the validation sets.

**a) Occlusal morphology. 1. Matching of trimmed tooth 16 to its respective arch–**The processed models and their trimmed original tooth 16 of the validation sets will be anonymized. The AI generated tooth 16 on these processed models will be used as a guide to match the trimmed original tooth 16 to its corresponding arch. The individual trimmed original tooth 16 will be best fit superimposed to the AI generated tooth 16 on these processed models. Hausdorff distance (HD) showing the degree of match will be obtained and the trimmed original tooth with the least HD will be regarded as best fitting and will be matched to this processed model [36]. The percentage of correct matching will be reported.

**2. The geometric morphometric of AI generated tooth**–the cusp tips (highest point), fossae (lowest point) and cuspal inclines (joining the cusp and fossa) of the individual cusps will be compared to the original tooth 16 by best-fit superimposition and their differences will be analyzed (Fig 7A).

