### Sample size determination

Each sample, training or validation set, of this study refers to the digitalized tooth model(s) collected from one participant. In a systematic review of the sample size determination for medical AI studies, only 4 studies provided rationale of sample size calculation [38], and only one study is about CNN and 3D images [39]. The recommended sample size for CNN in the medical imaging 3D computed tomography has been found to be 1000. From its Receiver Operating Characteristic (ROC) curve, the accuracy of AI system starts to reach plateau when the sample size reaches 200 and become saturated when reach 1000. Therefore, 200 subjects will be recruited as the minimal working sample size for training the AI system. More subjects that are eligible will be recruited for AI training if possible. Additional 50 subjects will be recruited for the validation sets.

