## Discussion

This is a prospective experimental study regarding artificial intelligence-designed dental prostheses, as well as one of the first few projects related to applying AI in Prosthodontics for replacement of single missing tooth. Its results may be proved crucial in future research into extended AI involvement in dentistry such as the use of specific GAN algorithm and the need of antagonistic teeth models may be used to further improve AI system for other prosthodontic procedures.

It is also yet an uncertainty on wide application of AI in various dental treatments due to the difficulties, including but not limited to standardization, repeatability, robustness and technical issues. The checklist of CONSORT-AI will be completed as supplement data when reporting the result of this study.

With sufficient resources devoted to the training of AI, like providing ample learning samples until the system is saturated and is no longer showing improvement, the outcome of the study may be different from the preliminary results. Receiver Operating Characteristic (ROC) curves will be plotted to determine the saturation/plateau of this AI system. Further studies will be conducted to examine the generalizability (external validity) of this AI system by including subjects who have received orthodontic treatments and/or with history of periodontal diseases in the validation sets. The limitation of this AI system includes teeth movement within periodontal ligament was not considered.

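### The 50 validation models are used both to choose the system and to report its accuracy, so the chosen system's accuracy is optimistic by a few points unless one algorithm is clearly best

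*Protocol article*

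**What the plan says.** All references are to the protocol article.

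- **Sample.** Under Collection of teeth models: "Maxillary and mandibular dentate teeth models will be collected from at least 250 volunteers". Under Sample size determination: "Therefore, 200 subjects will be recruited as the minimal working sample size for training the AI system" and "Additional 50 subjects will be recruited for the validation sets". Any further eligible recruits go to training.
- **Split.** Under Preparation of teeth models: "Collected teeth models will be randomly divided into" training and validation sets. No third set is named, and only training sets are described as input to the AI.
- **Choice of algorithm.** Under Validation of AI system: "Separate (50) sets of the original and the processed maxillary teeth models will be serve as validation sets". The four algorithms are evaluated against the natural tooth 16 on these models.
- **Choice of input.** The next step in that section is the antagonist question: "After determining the appropriate GAN algorithm, the need of antagonist mandibular teeth models in AI predicting the occlusal morphology".
- **Reported results.** Under Outcome measurement, the generated tooth is compared with the natural tooth in the validation sets. The percentage of correct matches is to be reported, and Hausdorff distance is used for matching and for contours. The indicators are read at least four times, "when 25%, 50%, 75% and 100% of collected teeth models have been learned respectively by the AI system".
- **Saturation.** The Discussion speaks of "providing ample learning samples until the system is saturated and is no longer showing improvement" and of judging a plateau, without naming the data used.

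**The concern.** The first objective asks how close the AI-generated tooth is to the natural one. The second and third ask which algorithm and which input to use. With only two sets, the 50 validation models have to serve all three. When several candidates are scored on the same 50 cases and the best is kept, part of its lead is chance. Quoting its score from those cases carries that chance into the performance estimate, so the matching percentage is too high or, if distance is the selection criterion, the Hausdorff distance is too small. A confidence interval computed on the 50 would not reveal this. The external validation foreseen in the Discussion concerns people with orthodontic treatment or periodontal disease, a different population, so it would not supply a clean estimate for the population studied here.

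**Working it through.** **1. The plan's own figure.** 200 training + 50 validation = 250, which agrees with the stated minimum. No model is left over for a separate test set. The article gives no expected accuracy, standard deviation or target precision, so the 50 cannot be derived from a formula.

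**2. Number of candidates.** Four algorithms are compared first. The antagonist input is then varied for the chosen one, which adds one configuration: 4 + 1 = 5.

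**3. Bias in the matching percentage.** Bias = expected value of the largest of k observed proportions on n = 50, minus the true rate p, with all candidates equally good. It was simulated with 20,000 replicates, using a latent correlation ρ between candidates on the same model. Both p and ρ are assumptions. Results are in percentage points for ρ = 0 / 0.5 / 0.8. The last column is the ordinary 95% half-width, 1.96 × √(p(1−p)/50).

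| True rate p | Best of 4 | Best of 5 | Half-width |
|---|---|---|---|
| 50% | 7.3 / 6.0 / 4.6 | 8.2 / 6.7 / 5.2 | 13.9 |
| 70% | 6.6 / 5.4 / 4.3 | 7.4 / 6.1 / 4.8 | 12.7 |
| 80% | 5.7 / 4.8 / 3.8 | 6.4 / 5.4 / 4.3 | 11.1 |
| 90% | 4.2 / 3.6 / 2.9 | 4.7 / 4.0 / 3.2 | 8.3 |

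Over the table, best of four gives 2.9 to 7.3 points and best of five 3.2 to 8.2. At 80% the bias is between 3.8/11.1 = 34% and 6.4/11.1 = 58% of the half-width.

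**4. Unequal algorithms.** Here bias = the winner's observed rate minus its own true rate, best of four, for the same three values of ρ.

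- True rates 80/75/75/70%: 4.6 / 3.4 / 2.2 points.
- True rates 80/60/50/40%: at most 0.2 points.

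**5. Continuous criterion, such as Hausdorff distance.** Bias = E[max of k standard normals] × SD × √((1−ρ)/50), with E[max] = 1.03 for k = 4 and 1.16 for k = 5.

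- k = 4: 1.03 × √(1/50) = 0.15 SD at ρ = 0, and 1.03 × √(0.2/50) = 0.07 SD at ρ = 0.8.
- k = 5: 1.16 × √(1/50) = 0.16 SD at ρ = 0, and 1.16 × √(0.2/50) = 0.07 SD at ρ = 0.8.

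**6. After the fix.** If the system is frozen before the 50 are scored, the expected selection bias is 0. The half-widths in the table are unchanged.

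**The case against.** - **The article never says that only the winner's score will be reported.** If all four algorithms are reported, each estimate is unbiased for its own algorithm and the paired comparison is sound. This stands. The bias attaches only to the selected system's score when it is offered as the trial's accuracy.
- **The antagonist sentence does not name the 50 models.** True. It is an inference from the section heading and from the absence of other held-out data.
- **No indicator is named as the selection criterion.** Also true. The figures apply to whichever indicator drives the choice. An indicator only loosely related to it would be biased less.
- **The size could be small.** It could, if one algorithm is plainly better (step 4).

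Three stronger readings are tempting, and the documents do not support them.

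- A reader might count eight candidates, four algorithms each with and without antagonist. The text is sequential, so about five are in play.
- A reader might multiply by the four checkpoints to reach 32. Outcome measurement describes these as readings of training progress and selects none. They add bias only if a checkpoint is chosen, or training is stopped, on the validation results. The Discussion's remark on saturation sets no such rule.
- A reader might take learning all of the collected models, in the Fig 1 legend and Outcome measurement, to mean that the 50 enter training. The article calls the 50 separate and inputs only training sets, so this is loose wording, not leakage.

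**Conclusion.** The point holds conditionally. The 50 validation models are the only held-out data. If the accuracy of a system chosen on them is reported from them, it is optimistic. With equally good algorithms and a true matching rate of 50 to 90%, the overstatement is about 3 to 7 percentage points for best of four and 3 to 8 for best of five, or about 0.07 to 0.16 SD for a continuous selection criterion. It is near zero if one algorithm is clearly superior. These sizes rest on assumed accuracies and correlations, because the article gives neither, and on the inference that the antagonist step uses the same 50. The direction does not depend on the assumed sizes. It should be settled before the 50 are first scored, because a set that has guided a choice cannot be made untouched again.

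**What to change.** 1. Name one selection criterion in advance that software can compute, for example matching by Hausdorff distance.
2. Choose the algorithm, then the antagonist input, and any stopping point, by cross-validation within the training models. Take any checkpoint reading that informs a decision from the held-out folds, not from the 50.
3. Retrain the chosen system on all training models, freeze it, and score it once on the 50 as the answer to the first objective. If a paired comparison of all four algorithms on the 50 is also wanted, run it after the freeze, report all four, and do not reopen the choice.
4. In the Fig 1 legend and Outcome measurement, count the checkpoints in training models instead of collected models, so that they agree with Preparation of teeth models and Validation of AI system.

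**Cost.** No new participants.

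- With five folds the sequential choice needs 4 × 5 = 20 fold trainings for the algorithm and 5 more for the second antagonist state, plus one final training: 26 in all, on the cluster already available. A full four-by-two grid (8 × 5 = 40 fold trainings) is not needed.
- With 200 training models each fold model learns from 200 × 4/5 = 160, fewer than the 200 that the article calls its minimum. This affects the selection stage only, since the final system is trained on all of them. Recruiting beyond 200 would ease it.
- Restricting selection to a software-computed criterion avoids repeating the virtual-articulator and visual assessments for every fold.
- The reported accuracy will probably be slightly less favourable.

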### Outcome measurement

The progress of the AI training will be evaluated with quartiles analysis. The following indicators of AI-designed prostheses will be examined at least 4 times during the training procedure, when 25%, 50%, 75% and 100% of collected teeth models have been learned respectively by the AI system. The morphology, i.e., geometric morphometric, and 3D positions, of tooth 16 designed by the trained AI system will be assessed by comparing to the corresponding natural teeth among the validation sets.

**a) Occlusal morphology. 1. Matching of trimmed tooth 16 to its respective arch–**The processed models and their trimmed original tooth 16 of the validation sets will be anonymized. The AI generated tooth 16 on these processed models will be used as a guide to match the trimmed original tooth 16 to its corresponding arch. The individual trimmed original tooth 16 will be best fit superimposed to the AI generated tooth 16 on these processed models. Hausdorff distance (HD) showing the degree of match will be obtained and the trimmed original tooth with the least HD will be regarded as best fitting and will be matched to this processed model [36]. The percentage of correct matching will be reported.

**2. The geometric morphometric of AI generated tooth**–the cusp tips (highest point), fossae (lowest point) and cuspal inclines (joining the cusp and fossa) of the individual cusps will be compared to the original tooth 16 by best-fit superimposition and their differences will be analyzed (Fig 7A).

**Fig 7 pone.0268535.g007:**
[figure not shown]
A & B: Superimposition of teeth for comparison (left). Measurement of the geometric morphology and 3D position by locating the anatomical landmarks of a tooth such as cusp tips and fossae as well as the center of a tooth (arrowed) respectively (right).

**3. Functional occlusal morphology**–the maxillary and mandibular teeth models will be mounted to a virtual articulator (exocad; DentalCAD, exocad) at average setting and the whole system is instructed to perform simulated jaw movements to determine if there is any occlusal interference [9, 37].

**b) 3D position.** The center (and its coordinate) of the AI generated tooth and the original tooth 16 will be determined by the software (Fig 7B). Using the adjacent teeth as reference area for best-fit superimposition, the buccal and lingual contours of the AI generated tooth and the original tooth will be compared, and their differences will be observed both visually as well as in HD.

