#### Biomimetic dental prostheses

By replacing the missing teeth, dental prostheses aim to restore appearance and oral functions of a patient, thus restore patient’s quality of life. The prevalence of single tooth loss is the most observed pattern of tooth loss. For the best prosthodontic prognosis and restoration of functions, dental prostheses should be biomimetic [5, 6] and thus adopt the occlusal morphology and 3D position of healthy natural teeth. These features sustain the functional equilibrium of dentition such as the bucco-lingual position as well as the occlusal relationships, and any disturbance to this equilibrium may result in pathology of the teeth and thus oral dysfunctions. It has always been a challenge to reconstruct original morphology on the dental prostheses, and treatment outcome tend to vary, subjecting to errors and failure [7]. Thus, a more personalized approach in designing prostheses is needed [8, 9].

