#### Artificial Intelligence (AI) as solution

The use of AI and dental robots are considered as the trend of automated digital dentistry that may reduce the manpower costs, and AI models have shown the potential of being a reliable tool on various dental treatment process [16, 17]. AI is defined as “the capability of a device to perform functions that are normally associated with human intelligence such as reasoning, learning, and self-improvement” [18]. With adequate trainings, AI may perform tasks that in the past require human intelligence, and in connection with this, AI may help designing dental prostheses. Since the teeth of an individual subject are controlled by the same genes (genotype) [19], and all teeth are exposed to mostly identical oral environment (phenotype), the occlusal morphologies and 3D positions of a subject’s teeth are inter-related. By taking reference to the natural dentition, the prostheses in questions should be able to retain the original functionality and to have no interference to the jaw movements. It is hypothesized that using a 3D Generative Adversarial Network (GAN) [20, 21], AI can learn the morphology and positional relationship between teeth in an individual subject and automate the design of biomimetic single-tooth dental prostheses from the features of the remaining dentition after sufficient trainings.

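### The only functional outcome records interference, so by itself it cannot penalise a generated tooth 16 that is out of contact with its antagonist

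*Protocol article*

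**What the plan says.** Outcome measurement lists three occlusal morphology outcomes and one position outcome. The functional one, item a)3, mounts the maxillary and mandibular models on a virtual articulator at average setting, and "the whole system is instructed to perform simulated jaw movements to determine if there is any occlusal interference". It names no reading of contact or clearance, and no run of the natural tooth 16 for comparison.

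Elsewhere the article describes function more broadly:
- The Introduction, on AI as a solution, says that "the prostheses in questions should be able to retain the original functionality and to have no interference to the jaw movements".
- On biomimetic prostheses it says of the natural tooth's morphology and position: "These features sustain the functional equilibrium of dentition such as the bucco-lingual position as well as the occlusal relationships". It adds that "any disturbance to this equilibrium may result in pathology of the teeth and thus oral dysfunctions".
- Under Presence of antagonist teeth models it says: "These antagonist models provide the information of occlusal contacts and limits the cuspal height of occlusal morphology". The same section says that the maxillomandibular relationship at MIP will be input to the system.

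Two other outcomes bear on height and shape. In item a)2, cusp tips, fossae and inclines "will be compared to the original tooth 16 by best-fit superimposition and their differences will be analyzed". In item b), "The center (and its coordinate) of the AI generated tooth and the original tooth 16 will be determined by the software", and the buccal and lingual contours are compared after registration on the adjacent teeth, by eye and by Hausdorff distance.

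**The concern.** A crown can fail functionally in two directions: too high, so that it interferes, or too low, so that it does not meet its antagonist. Item a)3 looks in one direction only. A tooth 16 with no contact at MIP gives the best result available, namely no interference found, and lowering the crown further never makes that result worse.

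This matters because Validation of AI system sets up two comparisons: first four algorithms, then training with versus without the mandibular model. On the functional outcome, a method that tends to make low crowns would look better than one centred on the true height. In the second comparison, part of what the antagonist is said to contribute, its contact information, is not read by the outcome closest to it.

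**Working it through.** **1. Aim against measurement.** The Introduction sets two requirements: original function kept, and no interference. Item a)3 tests the second. The antagonist is credited with two things: information on contacts, and a limit on cusp height. Item a)3 can detect a breach of the limit but not a loss of contact.

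**2. Do the other outcomes fill the gap?**

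| Outcome | Flat cusps | Crown too low, shape correct | Contact with antagonist |
|---|---|---|---|
| a)1 matching by Hausdorff distance | may show as a poorer fit | removed, because the natural tooth is fitted to the generated tooth | not measured |
| a)2 cusps, fossae, inclines | should show | removed if the fit is tooth to tooth; the registration area is not stated | not measured |
| a)3 interference | cannot count against the tooth | cannot count against the tooth | not measured |
| b) centre coordinate | may shift | should shift, but height is mixed with crown size | not measured |
| b) buccal and lingual contours | limited | may show, since registration is on adjacent teeth; the distance is unsigned | not measured |

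Flat and low teeth are thus partly visible elsewhere, but the last column is empty throughout.

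**3. Illustration of the one-sidedness.** The article gives no stated figure to reproduce on this point. Its one relevant number is the 50 validation sets. Everything else here is assumed: vertical error e in mm is normal with mean μ and standard deviation σ (positive = too high), a tooth interferes if e > 0.05, and it has no contact if e < −0.05.

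- Interference-free of 50 = 50 × Φ((0.05 − μ)/σ)
- No contact of 50 = 50 × Φ((−0.05 − μ)/σ)
- Within tolerance = the difference of the two

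Worked case, σ = 0.2:
- μ = 0: interference-free 50 × Φ(0.25) = 29.9; no contact 50 × Φ(−0.25) = 20.1.
- μ = −0.5: interference-free 50 × Φ(2.75) = 49.9; no contact 50 × Φ(2.25) = 49.4.

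| σ (mm) | μ (mm) | Interference-free | No contact | Within tolerance |
|---|---|---|---|---|
| 0.1 | 0 | 34.6 | 15.4 | 19.1 |
| 0.2 | 0 | 29.9 | 20.1 | 9.9 |
| 0.3 | 0 | 28.3 | 21.7 | 6.6 |
| 0.1 | −0.5 | 50.0 | 50.0 | 0.0 |
| 0.2 | −0.5 | 49.9 | 49.4 | 0.5 |
| 0.3 | −0.5 | 48.3 | 46.7 | 1.7 |

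Entries are rounded separately, so differences may be off by 0.1. At μ = −1.0, all 50 are interference-free and all 50 are out of contact at each σ.

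Read on interference alone, the lowered teeth come out ahead (48 to 50 against 28 to 35). Read two-sidedly, the order reverses (0 to 2 against 7 to 19). The counts depend on the assumed values. The direction does not: for any fixed σ and tolerance, Φ((0.05 − μ)/σ) rises as μ falls.

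**The case against.** The strongest reply is that item a)3 is one indicator among several and should not be read alone. Flattening is a shape difference that superimposition cannot remove, so item a)2 should show it. Registration on the adjacent teeth in item b) preserves a vertical offset, so a lowered crown shifts the centre and may widen the contour distance. This stands. It rules out the inference that a flat or low tooth would pass the whole outcome set.

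A reader might also infer that algorithms will be ranked on interference, or that the study could declare the antagonist unnecessary on the strength of teeth out of occlusion. The article does not support this. It defines no score, no category of functional success and no ranking rule, and it frames both comparisons by occlusal morphology and 3D position together. Nor does it suggest that the networks err low; they are trained on the natural models. That item a)2 hides a vertical offset is likewise only a possible reading, because its registration area is not stated and its figure is not available.

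Finally, the article is condensed, and the full protocol may say what the articulator session records. That is fair for operational detail. But the article does state what the simulation is meant to determine, and that criterion is one-sided. What survives is that no listed outcome measures contact, while the article's own account of function includes it.

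**Conclusion.** The point holds as a limited defect that is cheap to repair. Taken by itself, the functional outcome cannot count against a tooth 16 that does not meet its antagonist, and the other outcomes offer indirect and partial cover. The functional part of both comparisons is therefore one-sided, although the study's overall conclusions are not shown to be biased.

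The documents allow no estimate of the size. The counts out of 50 rest on an assumed normal vertical error, assumed means and standard deviations, and an assumed 0.05 mm tolerance. They show direction only. It would be tempting to say that about half of the 50 validation teeth would err short and be counted as successes, but that presumes symmetric error and a success category that the article does not have. It should not be cited as a finding.

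**What to change.** Extend item a)3. In the same virtual-articulator session, record whether tooth 16 has contact at MIP (number and location of contacts, or signed clearance) as well as whether it interferes. Do this for the generated tooth and for the natural tooth 16 of the same validation set, so that each generated tooth is judged against its own reference. Report out of contact and interfering as separate results for each algorithm and for training with and without the antagonist, and read them alongside the morphometric and position outcomes.

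The cost is a change of protocol wording, one extra read-out per mounted model and, if the natural tooth is not already articulated, one run per validation set (50 in all). The mandibular models and the MIP relationship are already part of the plan, so no new participants or scans are needed. The downside is that the functional result may look less favourable. If the full protocol already records contact, the article need only say so.
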